**BIOLOGICAL ACTIVITY**											
Treg		x	x		x		x		x	x	x
Lymphocytes phenotype		x	x				x			x	
Fecal and saliva samples (microbiota)			x				x			x	
Gut tissue			x				x			x	
CSF		x				x					
Peripheral biomarkers		x			x	x			x		x
**QUALITY OF LIFE ASSESSMENT**											
ALSAQ40		x				x					x

*(1) If not done at diagnosis or in the last 12 months*.

*FMT, Fecal Microbial Transplantation; M, Month; MRC, Medical Research Council; FVC, Forced Vital Capacity; BMI, Body Mass Index; ALSFRS-R, Revised ALS Functional Rating Scale; ECG, Electrocardiogram; CSF, Cerebrospinal Fluid; ALSAQ40, ALS Specific Assessment Questionnaire; W, week.*.

### Adverse Events and Safety

According to Directive 2004/23/EC (implemented in Italy with D.Lgs 191/2007):

– “Serious adverse event” (SAE) means any untoward occurrence associated with the procurement, testing, processing, storage, and distribution of tissues and cells that might lead to the transmission of a communicable disease, to death or life-threatening, disabling, or incapacitating conditions for patients or which might result in, or prolong, hospitalization, or morbidity (https://www.hta.gov.uk/policies/human-application-adverse-event-and-reaction-saears-reporting; http://www.sc-toolkit.ac.uk/displaycontent.cfm?widCall1=customWidgets.content_view_1&cit_id=84).– “Serious adverse reaction” (SAR) means an unintended response, including a communicable disease, in the donor or in the recipient associated with the procurement or human application of tissues and cells that is fatal, life-threatening, disabling, incapacitating, or which results in, or prolongs, hospitalization or morbidity (https://www.hta.gov.uk/policies/human-application-adverse-event-and-reaction-saears-reporting; http://www.sc-toolkit.ac.uk/displaycontent.cfm?widCall1=customWidgets.content_view_1&cit_id=84).

The existing studies suggest that FMT is a safe therapy, with few serious adverse events reported. There have been individual reports of peripheral neuropathy, Sjogren syndrome, idiopathic thrombocytopenic purpura, microscopic colitis, contact dermatitis, rheumatoid arthritis, obesity, bacteremia, and ulcerative colitis flare after FMT (24). In one meta-analysis, the overall incidence rate of adverse events after FMT was 28.5%. The commonest FMT-attributable adverse event was abdominal discomfort; also diarrhea, transient fever, nausea, vomiting, and constipation were other common symptoms associated to FMT (24, 28–31).

For these mild adverse events, investigators will treat symptoms according to the usual clinical practice. In case of symptoms that could be considered severe or life threating, the investigator will have to inform the sponsor immediately (within 24 h by fax using a SAE form) and second FMT round may be avoided accordingly to the local investigator's judgment. In accordance with the legislative requirements, Centers will be requested to report immediately from their awareness any SAE or SAR occurring during the trial and coordinating center will send Completed forms by email to Italian National Transplantation Center (CNT).

The coordinating Center will be responsible for appropriate AE reporting to the regulatory authorities (CNT) every 6 months; investigators will be responsible for reporting to appropriate Ethic Committee. In case of death, a clinical report will be prepared by the caring investigator together with SAE form; in case of autopsy, autopsy report will be added to study documentation.

The trial will be stopped in case of 30% excess in the treating group of the following AEs: peritonitis, upper gastrointestinal hemorrhage, sepsis, bacteremia. Instead, the next toxicities will be considered acceptable: diarrhea, abdominal cramping and pain, nausea, vomiting, flatulence, fever, constipation, dizziness, sore throat, rhinorrhea, bloating, nasal stuffiness, urinary infections, headache, mild/moderate blood cells alterations; elevated CRP, rashes, urticaria, dermatoses, dermatitis (mild/moderate severity), elevated aminotransferase/alkaline phosphatase, loss of appetite, colitis/gastroenteritis.

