## Abstract

**Background and Rationale:** Among the key players in the pathogenesis of Amyotrophic Lateral Sclerosis (ALS), microglia and T regulatory lymphocytes (Treg) are candidate cells for modifying the course of the disease. The gut microbiota (GM) acts by shaping immune tolerance and regulating the Treg number and suppressive function, besides circulating neuropeptides, and other immune cells that play in concert through the gut-brain axis. Previous mouse models have shown an altered enteric flora in early stage ALS, pointing to a possible GM role in ALS pathogenesis. Fecal Microbial Transplantation (FMT) is a well-known therapeutic intervention used to re-establish the proper microenvironment and to modulate enteric and systemic immunity.

**Methods:** We are going to perform a multicenter randomized double-blind clinical trial employing FMT as a therapeutic intervention for ALS patients (NCT0376632). Forty-two ALS patients, at an early stage, will be enrolled with a 2:1 allocation ratio (28 FMT-treated patients vs. 14 controls). Study duration will be 12 months per patient. Three endoscopic procedures for intestinal biopsies in FMT and control groups are predicted at baseline, month 6 and month 12; at baseline and at month 6 fresh feces from healthy donors will be infused at patients in the intervention arm. The primary outcome is a significant change in Treg number between FMT-treated patients and control arm from baseline to month 6. Secondary outcomes include specific biological aims, involving in-depth analysis of immune cells and inflammatory status changes, central and peripheral biomarkers of ALS, besides comprehensive analysis of the gut, saliva and fecal microbiota. Other secondary aims include validated clinical outcomes of ALS (survival, forced vital capacity, and modifications in ALSFRS-R), besides safety and quality of life.

**Expected Results:** We await FMT to increase Treg number and suppressive functionality, switching the immune system surrounding motorneurons to an anti-inflammatory, neuroprotective status. Extensive analysis on immune cell populations, cytokines levels, and microbiota (gut, fecal and saliva) will shed light on early processes possibly leading the degenerative ALS course.

**Conclusions:** This is the first trial with FMT as a potential intervention to modify immunological response to ALS and disease progression at an early stage.

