**Figure 1 F1:**
[figure not shown]
Picture of the study design.

The study will include 42 ALS patients with 2:1 allocation in 2 groups of subjects (28 FMT vs. 14 controls). Patients will be screened in the 15 days before baseline; then they will be randomly allocated to either FMT or control group. Randomization will be 2:1 (FMT: controls) and will be performed on line (using a computer-generated list of random number that will be centrally generated in the Statistical Unit). Given the heterogeneous ALS progression, patients will be stratified by ΔFS (progression rate), calculated at randomization according to Kimura et al. (25). Riluzole will be maintained during the entire study duration unless adverse events or patients' decision to withdraw. Endoscopic treatment will be performed within 21 days from randomization. Randomization number will not be re-used in any case. Estimated enrolment time is 18 months.

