As for clinical outcome measures, we will compare ALSFRS-R total score and subscores (bulbar, respiratory, gross, and fine motor) changes from baseline to each time point in treatment arm vs. control arm. Frequency of procedures (PEG, NIV, IV) will be compared from baseline to each time point in treatment vs. control arm. The comparison of clinical endpoint among arms will be carried out by using the logistic regression model. Results will be presented as odds ratios (OR) and 95%C.I. FMT will be considered effective in relation to controls whether the OR of positive results will provide a *p* < 0.05. Change in FVC during the study will be analyzed using a mixed model for repeated measures (MMRM). Difference between treatment groups and two-sided 95% CI will be estimated .Log-rank tests via Kaplan-Meier method will be employed to compare differences in tracheostomy-free survival between the two treatment arms (from onset and from randomization), while Cox's proportional hazard model will be used for adjusting for any possible unbalanced prognostic factors. Statistical significance will be set at 0.05 level for a two-tailed test. Last observation will be considered for patients with missing data.

Given the short duration of the study, an interim analysis of efficacy data is not scheduled. Nevertheless, to address safety concerns, a report including all relevant clinical data of patients will be sent by the Statistics Unit to an independent Data and Safety Monitoring Board for scheduled DSMB meetings (also through Skype) when 14 patients would have completed the second treatment and then every 6 months.

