All subjects, after comprehensive written and verbal information, will date and sign an approved Informed Consent Form (ICF) explaining rationale, procedures, duration, possible risks and benefits associated with the study. The patient will be informed that participation in the study is voluntary and that refusal to participate or withdrawal from the study, at any time, will not be associated to any penalty, or loss of benefits. An insurance company will provide insurance coverage for damages to patients involved in the trial. Principal Investigator will be supplied with all data concerning the insurance company and policy number. Finally, the data privacy and confidentiality will be treated according to European and Italian law. An Independent Ethics Advisory Board (IEAB) has been established, to address ethics concerns that could arise during the study, focusing especially to informed consent form. For this reason patient information sheet will be given to the candidate patient at least 15 days before the collection of the ICF. In the patient information sheet the patient will find a telephone number of the IEAB that he/she could call to have independent information. Furthermore, when the neurologist will give the patient information sheet to the patient, the investigator will advise IEAB of a possible enrollment to allow IEAB member to be present at the moment of the ICF collection. An independent Data Safety and Monitoring Board (DSMB) has been established too, to address safety and efficacy concerns that could arise during the study. Reports including all relevant clinical data of patients will be sent by the Statistics Unit of the University of Modena to the independent DSMB for scheduled DSMB meetings when 14 patients have done the second treatment and subsequently after every 6 months. All the partners will guarantee the dissemination and exploitation of the scientific results within the consortium and externally (international conferences, publications, dedicated workshops with patients). The results will be presented during national and international neurological and ALS meetings and workshops. Results will be published on www.clinicaltrials.gov and in peer-reviewed international journals.

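### The mandatory stopping rule on a 30% excess of four life-threatening events has no stated scale, and neither reading works as a safety boundary at 28 vs 14

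*Protocol article*

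**What the plan says.** The rule stands in the protocol article under Adverse Events and Safety: "The trial will be stopped in case of 30% excess in the treating group of the following AEs: peritonitis, upper gastrointestinal hemorrhage, sepsis, bacteremia". Study Design gives the arm sizes: "42 ALS patients with 2:1 allocation in 2 groups of subjects (28 FMT vs. 14 controls".

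The article describes four other safeguards:
- Serious events: "Centers will be requested to report immediately from their awareness any SAE or SAR occurring during the trial".
- Severe symptoms in a patient: the "second FMT round may be avoided accordingly to the local investigator" (at that investigator's judgment).
- The transplantation authority: "appropriate AE reporting to the regulatory authorities (CNT) every 6 months".
- An independent DSMB, set up "to address safety and efficacy concerns that could arise during the study" (Ethics Statement), with reports that start "when 14 patients would have completed the second treatment and then every 6 months" (Data Analysis).

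None of these carries a threshold or says when the mandatory rule is met. The article gives no expected rate for the four listed events. Controls also undergo endoscopy with biopsy: "Three endoscopic procedures for intestinal biopsies in FMT and control groups are predicted at baseline, month 6 and month 12". Procedure-related events are therefore possible in both arms.

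**The concern.** The sentence fixes both a number and a compulsory action, but the number has no scale. Two competent readers could give opposite instructions on the same data. With 3 of 28 FMT patients and 1 of 14 controls affected, the rates are 10.7% and 7.1%. That is a difference of 3.6 points (continue) and a ratio of 1.5 (stop).

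Choosing a scale does not solve the problem. With so few patients and presumably rare events, a 30-point gap is very large, and a ratio has no value until a control patient is affected. The events covered can kill. At stake is whether the one binding stopping criterion would respond to harm confined to the FMT arm.

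**Working it through.** **Inputs.** From the article: 28 FMT and 14 control patients, 30%, four events, 42 patients in 18 months. Assumed: each patient counts once, the four events are pooled, patients are independent, and true risks lie between 1% and 30%. The article states no operating figure for the rule, so there is none to reproduce. Let x be the FMT patients affected and y the controls affected.

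**1. Thresholds at full enrolment (no risk assumption needed).**
- Points: x/28 − y/14 ≥ 0.30, so x ≥ 8.4 + 2y.
- Ratio: (x/28)/(y/14) = x/(2y) ≥ 1.3, so x ≥ 2.6y for y ≥ 1; undefined at y = 0.

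| Controls affected | FMT patients needed, points | FMT patients needed, ratio |
|---|---|---|
| 0 | 9 | undefined (1 if any case against none counts) |
| 1 | 11 | 3 |
| 2 | 13 | 6 |

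On points, 8 of 28 against 0 of 14 is 28.6% and does not stop the trial. With 14 FMT patients and no control affected, x ≥ 0.30 × 14 = 4.2, so 5 are needed.

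**2. Points: chance of stopping when harm is confined to FMT.** One look at 28 vs 14, y = 0, P(X ≥ 9) with X ~ Bin(28, p):
- p = 10%: 0.1%
- p = 20%: 9.0%
- p = 30%: 47%

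With equal risk in both arms the points rule almost never fires: below 0.01% at 1% and 5% risk, 0.03% at 10%. The weakness on this reading is insensitivity, not false alarms.

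**3. Ratio: how often it is undefined.** P(no control affected) = (1 − p)^14:
- 1% risk: 87%
- 2% risk: 75%
- 5% risk: 49%

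The outcome then turns on how zero controls are handled. Chance of a stop with equal risk in both arms, by exact enumeration:

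| Risk in both arms | Any FMT case against none counts | It does not count |
|---|---|---|
| 1% | 21% | 0.03% |
| 5% | 43% | 5.9% |
| 10% | 42% | 21% |

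At 1% risk, the contribution from zero controls is 0.99^14 × (1 − 0.99^28) = 0.869 × 0.245 = 0.213, almost all of the 21%. If a zero-control excess does not count, the chance of stopping under FMT-only harm is 0% at any risk, because the ratio never exists.

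**4. When the DSMB first sees a scheduled report.** At even accrual (assumed) of 42/18 = 2.33 per month, and six months to the second procedure:
- 14 patients of either arm: 14/2.33 + 6 = month 12, with 28 randomised.
- 14 FMT patients (21 randomised at 2:1): 21/2.33 + 6 = month 15, with 35 randomised.

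The interval from randomisation to endoscopy would add a little to each.

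**5. An absolute count over both arms as the trigger.** Chance that the count is reached by trial end:

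| True risk | Count 2 | Count 3 | Count 4 |
|---|---|---|---|
| 1% both arms (n = 42) | 6.6% | 0.9% | 0.08% |
| 2% both arms | 21% | 5% | 1% |
| 5% both arms | 63% | 35% | 16% |
| 10% both arms | 93% | 80% | 62% |
| 10% FMT only (n = 28) | 78% | 54% | 31% |

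Under 10% FMT-only harm, a count of 3 is reached in 54% of trials, where the points rule is met in 0.1%. The two actions differ: the count leads to a pause and review, the rule to a stop.

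**The case against.** The strongest reply is that this is a journal article. The scale, denominator, pooling and timing of a safety boundary commonly sit in the full protocol or a DSMB charter, which are not shown. That stands as far as missing detail goes, and if the full protocol names the scale, the ambiguity is cured in a few words. It does not answer the rest: the article states a binding 30%, and that figure performs badly on either scale.

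The second reply is that patient protection does not hang on this sentence. Serious events are reported at once, the second FMT can be withheld, the authority receives six-monthly reports, and a DSMB may act below any threshold. This stands and lowers the severity.

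Third, the article gives no risks for the four events and expects few serious ones after FMT, so the higher assumed risks have no source in it. This also stands. The thresholds in step 1, however, need no risk assumption.

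A reader might go further in two ways that the article does not support:
- That the rule would end 21% to 43% of trials with equal risk. Those figures require any FMT case against no control case to count as a 30% excess, which the article does not say. Without that convention they are 0.03% at 1% risk and 5.9% at 5%.
- That one early case would stop the trial on the points reading, since 1 of 3 exceeds 30%. This needs a comparison by arm after every patient, and the article describes no such check.

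**Conclusion.** The concern holds in this form: the mandatory rule has no stated scale, and neither natural reading gives a usable boundary at 28 vs 14. On points it needs 9 affected FMT patients against no controls, and at full enrolment it would detect FMT-only harm of 10%, 20% or 30% with probability 0.1%, 9% or 47%. On a ratio it is undefined in the state that is likeliest when events are rare (87% at 1% control risk, 49% at 5%), and what it then does depends on a convention the article does not give.

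The result rests on patient-level counting, pooling of the four events and assumed risks. Severity is moderate. A reader might infer that the trial lacks safety oversight; the article does not support that, because other safeguards exist. The defect is that its one explicit stopping criterion adds little to them.

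**What to change.** Make the main trigger an absolute count: when a stated low number of patients in either arm has had a listed event, procedures pause and the existing DSMB meets to review the data by arm. Three is an example. The article offers no basis for one number, so the sponsor and DSMB should confirm it, using the table in step 5. The count can be kept without unblinding and also covers endoscopy harm in controls.

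If the 30% rule is kept, define it as a difference between arms in the percentage of patients with at least one of the four events, pooled. Apply it only after a stated minimum, such as 10 FMT patients treated, and label it a backstop. It stays insensitive: checked after every patient from the tenth FMT patient on, it would be met in 8% of trials at 10% FMT-only risk and 41% at 20% (simulation), and in 0.01% and 0.9% of trials at equal risks of 1% and 5%.

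The cost is two protocol sentences, with no new committee, visit or procedure. The downside is some DSMB reviews over chance events: with a count of 3 and equal risk, 0.9% of trials at 1% risk, 5% at 2%, 35% at 5% and 80% at 10%. A count of 3 also still misses 46% of trials with 10% FMT-only harm (1 − 0.54), so DSMB judgment remains necessary.

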### Data Recording and Data Monitoring

An electronic case report form (CRF) will be prepared for data recording.

A certified contract research organization (CRO) will be in charge for monitoring the study.

The study monitor indicated by the coordinating center will be in contact with the investigators and will conduct a visit to each Center to discuss and/or collect data. The Monitor will conduct a visit before the start of the study to discuss the protocol and obligations of the investigators and sponsor. Investigators of each center are required to allow the Monitor to conduct the site visit, the study-end visit and the site closure visit.

The Investigators will make all pertinent records available including original medical documents for inspection by regulatory authorities.

Copies of the protocol, subject identification codes, electronic Case Report Form, source data, Informed Consent Form and other documents related to the study conduction and support the data collected from each subject will be stored for the maximum period of time as required by the study centers. No study document should be destroyed.

Originals of all documentation and copies of outgoing correspondence concerning the study will be stored and retained by the Sponsor in a safe area in the Trial Master File.

### Role of Participating Centers

This multicenter study will involve nine Italian Units: six referral ALS Centers (located in Florence, Chieti, Perugia, Modena, and Rome), three renowned laboratories, one endoscopy service and a statistical unit.

ALS is a rare disease with fast progression and no effective treatment, which requires a solid methodological, clinical approach, and biological background for clinical trials conduction.

Each clinical center is expected: (I) to randomize at least seven patients according to including and excluding criteria in 18 months; (II) to provide one principal investigator to evaluate including and excluding criteria, and assess primary and secondary outcomes; (III) to adhere to ALS management guidelines of the European Federation of Neurological Societies(in particular as regards ventilation and nutrition issues).

The analysis of biomarkers will be centralized and performed in two internationally renowned laboratories Laboratory of Microbiology Policlinico Gemelli in Rome and Laboratory of Immunology, Department of Experimental and Clinical Medicine—University of Florence, and FMT will be performed at Policlinico Gemelli in Rome, a leading European Center for this kind of treatment.

### Data Analysis

Data will be collected by investigators through electronic CRF, which will be conveyed to the trial database. At trial completion, data from the locked database will be extracted for analysis by an expert statistician.

Separate analyses will be performed in:

All randomized subjects receiving at least 1 FMT (Intention-to-treat population).All randomized subjects excluding protocol deviations (Per protocol population).

As far as biological activity is concerned, immune response to FMT will be analyzed as a difference in positive response to FMT between the control group and the FMT group, assessed by comparison of proportion of patients in the two groups showing a mean Tregs increase by at least 20%, between baseline and month 6 measurements.

Mean values of different T, B, NK cell subpopulations, neurodegeneration biomarkers, and cytokines will be assessed and mean differences in plasma concentrations between the two treatment arms will be calculated using *t*-test or Wilcoxon-Mann-Whitney test as previously reported (26). ANOVA will be used for assessing the mean change over time for the same variables as above, with treatment as between-subjects factor and time as within-subjects factor. Different models will be used, each with a different biomarker of activity as the dependent variable. Models will be adjusted for any unbalanced distribution of the main prognostic factors (e.g., age) between the two treatment arms, according to previously published statistical methods (26).

Analysis of microbiota will be performed with specific software.

Record of any AE and SAE will be kept for every subject receiving at least one round of FMT till the study completion, performing safety analysis accordingly.

As for clinical outcome measures, we will compare ALSFRS-R total score and subscores (bulbar, respiratory, gross, and fine motor) changes from baseline to each time point in treatment arm vs. control arm. Frequency of procedures (PEG, NIV, IV) will be compared from baseline to each time point in treatment vs. control arm. The comparison of clinical endpoint among arms will be carried out by using the logistic regression model. Results will be presented as odds ratios (OR) and 95%C.I. FMT will be considered effective in relation to controls whether the OR of positive results will provide a *p* < 0.05. Change in FVC during the study will be analyzed using a mixed model for repeated measures (MMRM). Difference between treatment groups and two-sided 95% CI will be estimated .Log-rank tests via Kaplan-Meier method will be employed to compare differences in tracheostomy-free survival between the two treatment arms (from onset and from randomization), while Cox's proportional hazard model will be used for adjusting for any possible unbalanced prognostic factors. Statistical significance will be set at 0.05 level for a two-tailed test. Last observation will be considered for patients with missing data.

Given the short duration of the study, an interim analysis of efficacy data is not scheduled. Nevertheless, to address safety concerns, a report including all relevant clinical data of patients will be sent by the Statistics Unit to an independent Data and Safety Monitoring Board for scheduled DSMB meetings (also through Skype) when 14 patients would have completed the second treatment and then every 6 months.

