### Interventional Methods

Treatment will be double blinded to patients and neurologists, but not to the endoscopist and microbiologist. ALS patients will undergo upper GI endoscopy with small-intestine biopsies (*n*° 4 biopsies of small intestine, performed with a standard biopsy forces) at baseline and after 6 and 12 months. At baseline, the patients will be randomized (2:1) to either an allogenic (from donors) infusion of collected feces (60 grams) (FMT) in the duodenum-jejunum or no treatment (control group). The infusion will be performed through a standard nasojejunal tube that will be placed during endoscopy. Fecal infusion will be repeated at month 6. Control group patients will not receive any treatment (at baseline or at month 6), but will remain blind to treatment because of sedation due to small-intestine biopsies. Fecal microbiome will be diluted in saline solution (200 ml) and infused at 30 ml/min speed (whole amount of the performance: 15 min). Fresh feces for the FMT will be obtained by habitual healthy donors for *Clostridium difficile* infection. The Table 2 shows the blood and stool testing for donators and the general selection criteria. Before preparation, sample donation will be always analyzed by rapid molecular test to detect intestinal pathogens.

**Table 2 T2:** Criteria for donors' selection.

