### Sample Size Estimation

Sample size was calculated considering as primary outcome measure the proportion of patients, in the transplantation group with respect to controls, displaying a “positive response” intended as an increase in the proportion of Treg by at least 20%. The null hypothesis states that FMT does not ameliorate significantly the proportion of positive responses in treated patients after the second FMT round, compared to their baseline and to control group. The alternative hypothesis is that FMT gives a proportion of positive responses in at least 50% of treated patients compared to a maximum 5% of positive responses in patients of the control group. The study was designed to refuse the null hypothesis with an alpha error of 0.05 and a power of 0.80 according to previously published statistical methods (26) and to known levels of Tregs in ALS patients, that typically display a slight reduction of Treg % (mean ± standard deviation: 2.1 ± 0.7) with respect to healthy controls with fast progressors patients having on average 31% fewer Treg (8, 27).

For this purpose, a population of 39 patients randomized in two treatment arms would suffice; taking into account an average drop out of 10%, a recruitment of 42 patients will be needed.

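### The intention-to-treat set admits only patients who received an FMT, so it contains no controls and cannot support the randomised comparison

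*Protocol article*

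**What the plan says.** The article's Data Analysis section names two analysis sets. The first is "All randomized subjects receiving at least 1 FMT (Intention-to-treat population"). The second is "All randomized subjects excluding protocol deviations (Per protocol population"). No set of all randomised patients by allocated arm is defined.

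Interventional Methods describes the randomised choice as a donor infusion "in the duodenum-jejunum or no treatment (control group"), and adds: "Control group patients will not receive any treatment (at baseline or at month 6"). Controls have the sedation, endoscopy and biopsies only.

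The text under Figure 1 gives the design as "2:1 allocation in 2 groups of subjects (28 FMT vs. 14 controls") and the timing as: "Endoscopic treatment will be performed within 21 days from randomization".

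Data Analysis nevertheless plans comparisons between the arms throughout. For the Treg outcome, "immune response to FMT will be analyzed as a difference in positive response to FMT between the control group and the FMT group". The same section compares biomarkers, ALSFRS-R, FVC, procedures and tracheostomy-free survival between arms.

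**The concern.** An intention-to-treat set holds everyone randomised, in the arm to which they were allocated. The set defined here depends on having received the experimental treatment, which is an event after randomisation and one that only one arm can experience.

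Read as written, the set has no comparator, and the primary comparison cannot be computed in it. If an analyst silently adds the controls back, the rule becomes an exclusion in one arm only. An FMT patient who withdraws, deteriorates or becomes unfit before the infusion is removed, while an equivalent control is kept. In ALS such patients are likely to differ in prognosis from those who reach the procedure. For tracheostomy-free survival counted from randomisation, the rule also requires FMT patients to be event-free until the infusion, a small immortal-time bias in favour of FMT.

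The per-protocol set does not help. It includes controls but selects on conduct after randomisation, and as worded it does not separate major from minor deviations.

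**Working it through.** **Who qualifies for the set**

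| | Allocated (Study Design) | FMTs received under the protocol (Interventional Methods) | In the set |
|---|---|---|---|
| FMT arm | 28 | at least 1, unless never infused | 28 − k |
| Control arm | 14 | 0 | 0 |

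Here k is the number randomised to FMT but never infused. The set loses 14/14 = 100% of the comparator, and 14/42 = 33% of the trial, before k is counted. This result needs no assumption.

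**If controls are kept anyway**

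The set becomes 28 − k against 14. The documents give no value for k. As an illustration, suppose all of the 10% drop-out in Sample Size Estimation fell before the first infusion. Then k = 0.10 × 28 = 2.8, about 3 patients, with no matching removal among controls.

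**The plan's sample size**

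The inputs are responder rates of "at least 50% of treated patients compared to a maximum 5% of positive responses in patients of the control group", alpha 0.05 two-sided and power 0.80. The stated result is 39 patients, 42 with drop-out. With the pooled-variance formula for two proportions:

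- Equal arms: 14.2 per arm; with continuity correction 18.4, rounded up to 19, total 38. This is within 2 of 39.
- 2:1 allocation: 11.03 controls, rounded up to 12, total 36; with continuity correction 14.2, rounded up to 15, total 45.
- Drop-out: 39/(1 − 0.10) = 43.3, rounded up to 44, against 42 stated.

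So 39 is matched approximately, and only on the equal-allocation route. This does not affect the finding. At 2:1, 39 patients (13 vs 26) have power 0.87, above the target.

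**Does a true intention-to-treat set cost too much power?**

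Power = Φ[(p_T − p_C − 1.96 × SE0)/SE1], where

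- SE0 = √[p̄(1 − p̄)(1/14 + 1/28)], with p̄ the pooled rate;
- SE1 = √[p_C(1 − p_C)/14 + p_T(1 − p_T)/28].

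All 42 patients, everyone infused: p_C = 0.05, p_T = 0.50, p̄ = (14 × 0.05 + 28 × 0.50)/42 = 0.35. SE0 = 0.156 and SE1 = 0.111, so power = Φ[(0.45 − 1.96 × 0.156)/0.111] = Φ(1.30) = 0.90.

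Now keep k uninfused patients in the FMT arm and assume that they respond at the control rate: p_T = [(28 − k) × 0.50 + k × 0.05]/28.

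| k | p_T | Power, normal approximation | Power, Fisher's exact test |
|---|---|---|---|
| 0 | 0.500 | 0.903 | 0.906 |
| 1 | 0.484 | 0.880 | 0.884 |
| 2 | 0.468 | 0.853 | 0.858 |
| 3 | 0.452 | 0.824 | 0.829 |
| 4 | 0.436 | 0.792 | 0.795 |

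Power stays above the planned 0.80 for up to three uninfused patients and falls just below it with four.

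**The case against.** The best defence is that the wording is loose and the intention sound. Every planned analysis presupposes two arms, so nobody would really analyse zero controls. Table 3 uses FMT 1 and FMT 2 as visit headings, and the gut biopsies in those columns are taken in both arms. The authors may therefore have meant attendance at the first procedure visit. The exclusion would then apply to both arms. Since patients and neurologists are blinded, drop-out before that visit should not depend on allocation, and the bias would be much smaller than under a one-arm exclusion.

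This reading is plausible, but the text does not state it, and Interventional Methods says plainly that controls receive no treatment. Even if it is right, the set would be a modified intention-to-treat set under the wrong name. The same condition also recurs in Data Analysis, where adverse events are to be recorded for those given at least one round of FMT, although Outcome Measures assesses safety in both arms and the stopping rule refers to an excess in the treated group.

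Three limits do stand. The per-protocol set still compares the arms, so the claim that no comparison remains applies to the intention-to-treat set only. The figure of about 3 of 28 is illustrative: the 10% is a planning average for the whole study, and the windows in Table 3 may shorten the gap before infusion. Finally, which deviations lead to exclusion from the per-protocol set may be settled in the full protocol or SAP.

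**Conclusion.** The concern holds. This is a definition that is wrong as stated, not detail left to another document. Under it, 0 of 14 controls and 28 − k of 28 FMT patients form the set, and the primary comparison cannot be made there. If controls are tacitly kept, the comparison depends on treatment received in one arm only. The size of the resulting bias cannot be computed, because the documents give no rate of drop-out before infusion; in a trial of 42, two or three exclusions could matter.

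The 0-of-14 count rests on the text alone. The power figures rest on the plan's rates of 5% and 50% and on the assumption that uninfused patients respond at 5%. If they were instead all counted as non-responders, power would be slightly lower. The point must be fixed before analysis, because it concerns the population for the primary comparison.

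**What to change.** Replace the two definitions with wording such as:

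- Intention-to-treat: all randomised patients, analysed in the arm to which they were allocated, whether or not any infusion was given. This is the primary analysis set.
- Per protocol: the intention-to-treat set without patients who have major deviations from a list fixed in advance and judged before unblinding. This set is supportive.

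If a set of treated patients is also wanted, define it by a step common to both arms, such as the baseline endoscopy, and call it modified intention-to-treat. Reconcile the sentence on recording adverse events in Data Analysis with Outcome Measures, so that both arms are covered.

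The cost is two sentences in the protocol and SAP, plus the safety wording. No extra patients or data are needed, and on the assumptions above power remains about 79% to 90% with zero to four uninfused FMT patients.
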